## Abstract

**Methods/design::**

This is a prospective 2-center, assessor and statistician blinded, randomized, controlled trial. We will allocate 106 subjects aged between 45 and 65 years old, diagnosed with aspirin semi-resistance after stroke to 2 groups randomly in a ratio of 1:1. Patients in the experimental group will be treated with conventional treatments plus *Panax notoginseng (Sanqi*) while the others in the control group will be treated with only conventional treatments. All will be given different medications for 30 days. Patients will be measured with the platelet aggregation rate and serum TLR4, MyD88, NF-*κ*B, COX-2, IL-6, CRP, TXB2 level for clinical efficacy and mechanisms at baseline and the 14^th^, 30^th^ day of treatment. Baseline characteristics of patients will be summarized by groups and compared with Chi-square for categorical variables, and Student’s independent *t* test or nonparametric Mann-Whitney *U* test for the continuous variables. Primary and secondary outcomes will be analyzed with 2-way repeated measures Anova, and Post Hoc test.

**Conclusion::**

The present study aims to investigate short-term add-on efficacy and mechanism of *Panax notoginseng (Sanqi*) for aspirin resistance in secondary stroke prevention via TLR4/MyD88/NF-κB signaling pathway. With this, we expect to find out an appropriate partial substitute of aspirin for aspirin resistance individuals.

**Trial Registration::**

The trial was registered on Chinese Clinical Trial Registry (http://www.chictr.org.cn/index.aspx) with the ID ChiCTR2100045773 at April 24, 2021.

## 1. Introduction

Despite the rapid development of medicine, stroke is still a major cause of death worldwide.^[1]^ Platelet activation still plays an important physio-pathological role in cerebrovascular thromboembolism events. Therefore, antiplatelet drugs, especially aspirin, play a vital role in the secondary stroke prevention.^[2]^ Since the 1990s, it has been found that about 5% to 60% patients still exist stroke recurrence when taking aspirin orally in clinical practice. This phenomenon has been called “aspirin resistance (AR)^.^”^[3]^ Currently, AR is divided into clinical AR and laboratory AR. Clinical AR refers to that it failures to inhibit thromboxane A2 (TXA2) production and TXA2- dependent platelet aggregation after regular aspirin administration. Laboratory AR is defined as arachidonic acid -induced mean platelet aggregation rate ≥ 20% and adenosine diphosphate -induced mean platelet aggregation rate ≥ 70%. Those who meet 1 of above 2 criteria are aspirin semi-resistance (ASR) ones.^[4]^ It has been reported that AR may increase the risk of recurrent cerebrovascular events by 2 times and the risk of death by 3.5 times,^[5]^ which brings heavy economic burden to the society and families.

Mechanisms of AR are multiple and complex, including clinical, genetic, pharmaco- logical, and biological factors.^[4]^ How to enhance bioavailability to overcome AR, there is no unified standards. It may mainly increase dose and frequency of drug, or combine with other antiplatelet drugs, which are lack of effective medical evidence,^[6]^ and increase risk of hemorrhage. Therefore, it’s urgent to find a safe and effective partial substitute of aspirin for AR individuals.

Studies have shown that some activating blood and removing stasis herbs medicine have a good prospect for AR.^[7]^ Long-term clinical observation, *Panax notoginseng (Sanqi*) can improve platelet aggregation rate of stroke patients with AR. However, whether it is effective for AR patients and how it works need to be further studied. Based on the current cases analysis, aspirin combined with *Panax notoginseng (Sanqi*) powder, which reduce platelet aggregation rate, serum TXB2 level and increase PGI2 level, is superior to aspirin alone among AR patients. Besides, literatures about the relationship between inflammation and TLR4/MyD88/NF-*κ*B signaling pathway of activating blood and removing stasis herbs medicine in AR are a growing.^[8]^ Moreover, *Panax notoginseng (Sanqi) shows* the anti-inflammatory and antiplatelet effect in experimental study.^[9]^ Thus, we proposes that *Panax notoginseng (Sanqi*) may reduce IL-6, COX-2 and TXA2 level to improve AR by regulating the inflammatory TLR4/MyD88/NF-*κ*B signaling pathway, so as to clarify the specific mechanism of *Panax notoginseng (Sanqi*) for AR and provide a new clinical molecular target for AR.

The primary objective of this study aims to investigate short-term add-on efficacy and mechanism of *Panax notoginseng (Sanqi*) for aspirin resistance in secondary stroke prevention via TLR4/MyD88/NF-*κ*B signaling pathway with a more strictly randomized controlled trial (RCT).

## 2. Methods/design

### 2.1. Study design

This is a prospective 2-center, assessor and statistician blinded, randomized, controlled trial with a parallel 2-arm group from June 2021 to May 2023. This study protocol is draw up based on Recommendations for Interventional Trials (SPIRIT) 2013 statement.^[10]^ The SPIRIT checklist will be presented in (Table S1, Supplemental Digital Content, http://links.lww.com/MD/H991). A total of 106 participants will be randomized into 2 groups at a ratio of 1:1. Participants in the treatment group will be treated with conventional treatments plus *Panax notoginseng (Sanqi*). Participants in the control group will be treated with conventional treatments.

The whole study period is 35 days, including 5-days baseline observation, 30-days treatment. Subjects will be measured with the platelet aggregation rate and serum TLR4, MyD88, NF-*κ*B, COX-2, IL-6, CRP, TXB2 level for clinical efficacy and mechanisms at baseline and the 14^th^, 30^th^ day of treatment. (Fig. 1, Table 1).

**Table 1 T1:** Schedule of enrollment, interventions and assessments.

Study procedure	Study period		
	Enrollment（d）	treatment period （d）	
Timepoints	-5^th^-0d	14^th^d ± 1d	30^th^d ± 1d
Enrolment			
Demographics	X		
Vital signs	X		
Medical history	X		
Complications	X		
Eligibility screen	X		
PHQ-9	X		
GAD-7	X		
MMSE	X		
Informed consent	X		
Random allocation	X		
Interventions			
Conventional treatments + Panax notoginseng		X	X
Conventional treatments		X	X
Assessments			
Platelet aggregation rate	X	X	X
TLR4, MyD88, NF-*κ*B, COX-2, IL-6, CRP, TXB2	X	X	X
Coagulation function	X	X	X
Safety evaluations	X	X	X
Patient compliance	X		
Drug combinations	X		
Adverse events	X		
Research summary	X		
Review statements	X		

GAD = generalized anxiety disorder, MMSE = mini-mental state examination, PHQ = patient health questionnaire.

**Figure 1. F1:**
[figure not shown]
Participant flowchart.

The clinical trial results will be reported according to the Standards for Reporting Interventions in Clinical Trials of Chinese Herbal Medicine Formulae 2017 (CONSORT-CHM extension 2017) statement.^[11]^

### 2.2. Ethics

The study protocol (version: V1.0) has been approved by the ethics committee of *Xi’an Hospital of Traditional Chinese Medicine (Xi’an Affiliated Hospital of Shaanxi Provincial Hospital of Chinese Medicine*) (approval NO.: LLSCPJ2021008) at May 18, 2021, and registered on http://www.chictr.org.cn/index.aspx developed by the Chinese Clinical Trial Registry with the ID ChiCTR2100045773 at April 24, 2021. Informed consents will be obtained from all the subjects involved. Any modification of the study protocol or informed consent that may affect the rights and interests of the participants or the implementation of this trial shall be reported to the Ethics Committee for approval. In case of any serious adverse event (AE) in the trial, the ethics committee shall promptly review it and recommend written modifications, including sufficient authority to suspend the trial.

### 2.3. Study population

#### 2.3.1.
*Inclusion criteria*.

1.Subjects, diagnosed with ischemic stroke, according to the *International Classification of Diseases (ICD-11, 8B11*),^[12]^ and *Chinese Guidelines for Diagnosis and Treatment of Acute Ischemic Stroke 2018*;^[13]^

2. Subjects, diagnosed with aspirin semi-resistance, according to 0.5 mmol/L arachidonic acid-induced mean platelet aggregation rate ≥ 20%, or 10*μ*mol/L adenosine diphosphate-induced mean platelet aggregation rate ≥ 70%;^[4,14]^

3. Subjects, aged between 45 and 65 years old, male or female;

4. Subjects, predicted in the low-risk profile of recurrent stroke, Essen stroke risk scores ≤ 3 points;^[15]^

5. Only taking single antiplatelet drug, not overlapping the use of activating blood and removing stasis herbs medicine;

6.Sign the informed consent forms.

#### 2.3.2.
*Exclusion criteria*.

1.Subjects, diagnosed with transient ischemic attack or cerebral infarction who need to take 2 antiplatelet drugs;

2. Cerebral infarction combined with cerebral hemorrhage, cerebral arteritis, brain tumor, brain trauma, brain parasitic disease, and rheumatic heart disease, et cetera;

3. With bleeding tendency or severe bleeding symptoms within 3 months;

4. With severe kidney and liver function insufficiency & hematopoietic and metabolic diseases;

5. With disabilities, such as blindness, deafness, dumb, mental disorders (depression [patient health questionnaire-9 scores ≥ 20points], anxiety [generalized anxiety disorder-7 scores ≥ 19points], cognitive dysfunction [mini-mental state examination scores＜17 points])^[16,17]^ and non-stroke physical disabilities;

6. Abuse of alcohol and (or) drugs, or other conditions that affect compliance;

7. Participation in any other clinical trial in recent 3 months.

#### 2.3.3.
*Withdrawal criteria*.

1.Violation of the inclusion criteria & clinical trial protocol;

2. Receive < 50% of treatment sessions;

3. Serious AEs or deterioration of stroke;

4. Withdraw the signed informed consent by subject or legal representative;

5. Replace the treatment protocol and (or) receive other unrelated treatments that could affect the study results.

### 2.4. *Study settings and recruitments*

The present study will be conducted in the Xi’an Hospital of Traditional Chinese Medicine (Xi’an Affiliated Hospital of Shaanxi Provincial Hospital of Chinese Medicine) and Shanxi Provincial Hospital of Chinese Medicine (Shaanxi Academy of Traditional Chinese Medicine).

Cerebral infarction patients with ASR in accord with the inclusion-exclusion criteria will be recruited at above-mentioned 2 hospitals, who mainly come from hospital wards & clinics. In addition, posters, leaflets and routine free clinics (every month) will be also helpful. Sure, the hospital websites, WeChat, and Microblogging are powerful advocacy media.

### 2.5. *Study group*

106 participants who meet above-mentioned criteria with signed informed consents will be selected. The subjects will be randomly divided into 2 groups in a 1:1 ratio, namely the experimental group and control group, 53 cases in each group.

### 2.6. *Study time*

This trial will be conducted from June 1, 2021 to May 31, 2023.

### 2.7. *Interventions*

Interventions are selected base on the theory of blood stasis in traditional Chinese medicine (TCM) and experience of experts.^[18]^ The traditional Chinese physicians involved have received their practitioners’ license from China’s National Health and Family Planning Commission, who have worked for more than 3 years. Subjects in experimental group will receive conventional treatments plus *Panax notoginseng (Sanqi*), and others in control group will just receive conventional treatments. Besides, if bleeding events or drug allergy happen during period, antiplatelet drug adjustment would be allowed.

#### 2.7.1.
*Experimental group*.

##### 2.7.1.1.
*Conventional treatments plus panax notoginseng (Sanqi*).

During the study period, patients will be given conventional treatments for ischemic stroke according to the *Guidelines for Secondary Prevention of Ischemic Stroke and transient ischemic attack in China (2014 edition*),^[19]^ such as taking an antiplatelet agent, anti-hypertensive drugs, lipid-lowering drugs, antidiabetic agents, intravascular treatments, folic acid and vitamins, et cetera. Nutritional support will be also allowed.

*Panax notoginseng (Sanqi)*, as a typical TCM, is recommended for the secondary prevention of cerebral infarction with blood stasis syndrome in the *Diagnosis and Treatment Guidance for Blood Stasis Syndrome by Integrative Medicine*^[18]^ and *Evidence-based practice guideline on integrative medicine for stroke 2019* (level of evidence: 2C).^[20]^
*Notoginseng* powder (云YPBZ-0091-2008, 3g, Yunnan Qiangfa Pharmaceutical Co. LTD, Kunming, China) will be administered after dissolved, 1 bag (3g) each time, once a day. Participants will be treated once a day for 30 consecutive days.

#### 2.7.2.
*Control group*.

##### 2.7.2.1.
*Conventional treatments*.

Patients in control group will be given conventional treatments mentioned above for ischemic stroke as same as the experimental group, once a day for 30 consecutive days.

### 2.8.
*Adverse events observation*

It could be that patients with xerocheilia, irritability, bleeding symptoms, et cetera are more likely related to investigational medications. With the patients diary, all AEs are to be recorded and measured during treatment period. Serious AEs should be reported to the principal investigator (PI) immediately. All details will be documented, antiplatelet drug adjustment, as well as appropriate medical care will be given at once. For the subjects with severe stroke during study, they would be considered as drop outs.

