### 2.10. Secondary outcomes

The secondary outcome will be the change of coagulation function for platelet assay and hemorrhage risk of stroke patients at 0 day, 14^th^ day and 30^th^ day of treatment. In addition, changes in liver and kidney function will be also tested for the medication safety in patients pre-and post-treatment. Their blood glucose, blood lipids, blood pressure, AEs and others will be tracked in patients diary during period. All the dropouts and causes will be documented in case report forms.

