### 2.13. Statistical analysis

Data analysis will be based on the full analysis set and per-protocol set in the light of data missingness (last-observation-carried-forward [LOCF] method) and robustness of our analytical results. All data will be analyzed using IBM SPSS Statistics 21.0 (v21.0, IBM Corp., Armonk, NY). Descriptive statistics will be performed with means ± standard deviations or median [interquartile range]. Baseline characteristics of patients will be summarized by groups and compared with Chi-square for categorical variables, and Student’s independent *t* test or nonparametric Mann-Whitney U test for the continuous variables. Primary and secondary outcomes are applicable to 2-way repeated measures Anova, and Post Hoc test will be for multiple comparisons between groups and time-points. If there is a violation of distribution assumption, appropriate transformation will be used. A *P* value < 2- sided 0.05 will be considered as significant.

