#### 2.13.3.
*Safety evaluation*.

The number (n) and percentage (%) of participants with AEs recorded in the diary will be calculated and compared using Chi-square test.

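### Post-randomisation events trigger withdrawal or dropout without separating stopping study treatment from leaving the study, so later samples may be lost and strokes may go uncounted

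*Protocol article*

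**What the plan says.** Section 2.3.3 of the protocol article lists the withdrawal criteria. Besides withdrawal of consent they include "Violation of the inclusion criteria & clinical trial protocol", "Receive < 50% of treatment sessions", "Serious AEs or deterioration of stroke", and replacing the treatment protocol or receiving other treatment that could affect the results. Section 2.8 adds a further rule: "For the subjects with severe stroke during study, they would be considered as drop outs".

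Other sections bear on what happens to these patients:

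- Section 2.13 names two analysis sets and one method for missing data: "Data analysis will be based on the full analysis set and per-protocol set in the light of data missingness (last-observation-carried-forward [LOCF] method".
- Section 2.8 also states that "all AEs are to be recorded and measured during treatment period" and that serious adverse events go to the principal investigator immediately.
- Section 2.10 requires that "All the dropouts and causes will be documented in case report forms", and Section 2.14 repeats that dropout reasons are recorded.
- Section 2.13.3 describes the only between-group safety comparison: the number and percentage of "participants with AEs recorded in the diary will be calculated and compared using Chi-square test".
- Sections 2.7 and 2.8 permit antiplatelet adjustment after bleeding, drug allergy or serious adverse events.

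No section says whether a withdrawn patient still gives the day-14 and day-30 samples.

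**The concern.** Low exposure, serious adverse events, stroke deterioration, replaced treatment and severe stroke can arise only once treatment is under way, and treatment can influence each of them. If they end a patient's participation, missing data become linked to both treatment and outcome.

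Unequal withdrawal between arms is plausible, though not stated. Only the experimental arm has a study product added to usual care, so the 50% exposure rule need not act alike in both arms. Patients know their allocation (Section 2.12), and only assessors and the statistician are blinded (Section 2.1). A criterion as broad as protocol violation can therefore be applied with knowledge of the arm.

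Two things are at stake. The first is the randomised comparison of platelet aggregation. The second, in a secondary stroke prevention population, is whether every new or worsening stroke reaches the safety comparison.

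**Working it through.** **1. The plan's own allowance for losses (Section 2.11).** The plan has 96 evaluable patients (48 per arm), 10% attrition and 106 recruited (53 per arm). 96 × 1.10 = 105.6, rounded up to 106, which reproduces the stated figure. Dividing instead, 96 / 0.90 = 106.7, gives 107, one more. The allowance is 106 − 96 = 10 patients, or 10/106 = 9.4%, about five per arm.

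**2. What carrying forward does with three time points.** Aggregation is measured at baseline, day 14 and day 30.

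| Last sample taken | Values analysed (baseline, day 14, day 30) |
|---|---|
| Baseline only | baseline, baseline, baseline |
| Day 14 | baseline, day 14, day 14 |

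In both rows the filled-in value predates the event that caused withdrawal. Entry requires high aggregation (Section 2.3.1: at least 20% with arachidonic acid or at least 70% with adenosine diphosphate), so a carried-forward baseline is likely to be high through selection.

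**3. Illustration of size.** Let k patients in one arm of 53 be affected. Let D be the gap between the carried value and the value that would have been measured. The arm mean at that visit shifts by k × D / 53. The same formula holds if the patients were left out altogether, with D then the gap between those left out and those retained. The documents give neither k nor D. Assume k = 5 (the whole attrition allowance of one arm, all due to these rules, none in the other arm):

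| Assumed D (points) | Shift in arm mean |
|---|---|
| 5 | 5 × 5 / 53 = 0.5 |
| 15 | 5 × 15 / 53 = 1.4 |
| 30 | 5 × 30 / 53 = 2.8 |

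The planned difference is 14, read here as percentage points. The middle row is 1.4/14, about a tenth of it.

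**4. Set against random error.** The article gives no standard deviation. Back-solving from one-sided 0.05, 80% power, 48 per arm, a difference of 14 and correlation 0.7 over three visits, the variance factor is (1 + 2 × 0.7)/3 = 0.8. Then SD = 14 / [(1.645 + 0.842) × √(2/48) × √0.8] ≈ 30.8. The standard error of the group difference is 30.8 × √(0.8 × 2/48) ≈ 5.6, so a shift of 1.4 is about 1.4/5.6 = 0.25 of a standard error. On the same SD, power is about 83% with 53 per arm, 80% with 48, 78% with 45 and 76% with 43. Loss of power is modest; the issue is bias.

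**5. The safety count.** A stroke classed as a dropout under Section 2.8 has its cause written in the case report form (Section 2.10). The comparison in Section 2.13.3 draws on the patient diary. Nothing links the two, and a patient with a severe stroke may be unable to keep a diary. If one stroke were missed, that arm's rate would change by 1/53 = 1.9 percentage points.

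**6. Sections that do not fit together.** Sections 2.7 and 2.8 permit antiplatelet adjustment after certain events. Section 2.3.3 withdraws patients with serious adverse events and those whose treatment is replaced. Whether a patient with a bleed and a permitted adjustment remains in the study cannot be determined from the text.

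**The case against.** A reader might infer that the plan removes these patients from efficacy and safety. The documents do not support that. Section 2.13 names a full analysis set with carry-forward, so on its face these patients are imputed, not deleted. Exclusion from a per-protocol set is what such a set is for. On safety, Section 2.8 has all adverse events recorded and serious ones reported, and Sections 2.10 and 2.14 have dropout causes documented. An event that triggers withdrawal occurs before the withdrawal and can still be counted.

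It can also be said that membership of the full analysis set, follow-up after withdrawal and the safety population are details that a journal article leaves to a fuller document. That is fair for the definitions, and their absence is not the point here. The withdrawal and dropout rules, however, are stated in the article, and no later analysis plan can recover blood that was never drawn.

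Finally, the numerical illustration is constructed. It puts every loss in one arm, attributes all attrition to these rules and assumes the gap. Unequal action of the 50% rule is likewise plausible and not written down: the rule names no arm, and the control group also has daily treatment for 30 days. Both objections stand, so the figures show scale only.

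**Conclusion.** The point holds as a risk created by stated rules. Events that treatment may affect are grounds for withdrawal or dropout, with no line drawn between ending study treatment and ending participation. The consequences are possibly missing day-14 and day-30 samples, carried-forward values from before the event, probable exclusion from the per-protocol set, and a diary-based safety count that may miss a stroke or serious adverse event logged elsewhere.

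The size of the bias cannot be computed from the documents. Under the assumptions shown (five patients, one arm, gaps of 5 to 30 points), it is 0.5 to 2.8 points against a planned 14. One uncounted stroke would be 1.9 percentage points of an arm. This is moderate and worth correcting because the correction is cheap.

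**What to change.** 1. In Sections 2.3.3 and 2.8, separate discontinuing study treatment from withdrawing from the study. State that the already scheduled day-14 and day-30 samples are collected from all randomised patients unless consent is withdrawn.
2. In Section 2.13, state that all randomised patients stay in the full analysis set in their assigned arm. Use adherence and protocol violations only to define the per-protocol set.
3. Replace the dropout sentence in Section 2.8 with one saying that a severe stroke during the study is recorded as an event and counted in the assigned arm, and that the patient remains in the full analysis set.
4. In Section 2.13.3, count strokes, stroke deteriorations and serious adverse events by arm from any source: diary, case report form or serious adverse event report.
5. Reconcile Sections 2.3.3, 2.7, 2.8, 2.13 and 2.13.3, including permitted antiplatelet adjustment against withdrawal for replaced treatment. These changes concern data collection and analysis; when treatment should stop is left to the investigators.

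The cost is protocol wording and a few more follow-up contacts for blood draws already scheduled. Sampling will not always be feasible after a severe stroke, so some values will still be missing.
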